### Interventions

Eligible patients who have signed informed consent will be randomized by the coordinating investigator in a 1 : 1 ratio using a software randomization program (ALEA Clinical; FormsVision, Abcoude, the Netherlands). Patients will be stratified for previous chemotherapy, previous radiotherapy, and expert centre. After randomization, the treating surgical oncologist will refer the patient to the medical oncologist (experimental arm) or radiation oncologist (control arm).

The study flow chart is shown in *Fig. 1*, and study interventions and timelines for patients allocated to the experimental and control arms in *Tables 1* and *2* respectively.

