**Fig. 1 zrab029-F1:**
[figure not shown]
Study flow chart B, blood samples for translational research; Q, questionnaires; CEA, carcinoembryonic antigen.

**Table 1 zrab029-T1:** Schedule interventions and assessments experimental arm

	Before allocation	After allocation			Follow-up	
	Outpatient clinic	Induction chemotherapy	Chemoradiotherapy	Surgery	Years 1–3	Years 4–5

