#### Questionnaires

All participants will be asked to provide separate informed consent to receive validated quality of life questionnaires (European Organisation for Research and Treatment of Cancer QLQ-C30 and QLQ-CR29; EuroQol EQ-5D-5L™ (EuroQoL Group, Rotterdam, the Netherlands)). Patients will receive questionnaires at inclusion, and 3 and 12 months after surgery either by mail or digitally, according to their own preference.

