### Outcomes

The primary outcome of the study is the proportion of patients with a clear resection margin. A resection margin is considered clear (R0), if there are no tumour cells in any of the resection surfaces as determined by microscopy (resection margin more than 0 mm).

Secondary outcomes are:

3- and 5-year local re-recurrence-free survival, defined as the interval between surgery and local re-recurrence;3- and 5-year progression-free survival, defined as the interval between randomization and progression of local recurrence, local re-recurrence, distant metastases or death;3- and 5-year metastasis-free survival, defined as the interval between randomization and development of distant metastases;3- and 5-year disease-free survival, defined as the interval between surgery and local re-recurrence, distant metastases or death;3- and 5-year overall survival, defined as the interval between randomization and death;pathological response, graded according to the Mandard grading system^40^;radiological response, scored according to the magnetic resonance tumour regression grade (mrTRG);compliance rate with induction chemotherapy (i.e., the number of patients receiving CAPOX, FOLFOX or FOLFIRI as initial regimen will be tabulated, and dose modification and reason will be summarized for each regimen);toxicity of induction chemotherapy, scored from day 1 of the first cycle of induction chemotherapy until 1 month after the final administration, and graded according to the Common Terminology Criteria for Adverse Events (CTCAE) version 5.0;compliance rate with chemoradiotherapy, calculated as the total radiotherapy dose received divided by the total planned dose;toxicity of chemoradiotherapy, scored from start of radiotherapy until 3 months after the final dose of radiotherapy, and graded according to CTCAE version 5.0;number of patients undergoing surgery;surgical characteristics (e.g., type of resection, ostomy, use of intraoperative radiotherapy, blood loss, duration of operation, intraoperative complications);major surgical morbidity rate scored from the date of surgery to 3 months after surgery, and graded according to the Clavien–Dindo classification^41^;quality of life, assessed with EQ-5D-5L™, QLQ-C30 and QLQ-CR29 questionnaires at inclusion, and at 3 and 12 months after surgery; andcost-effectiveness and cost–utility, based on Dutch costing guidelines for healthcare, the case report forms, and the EQ-5D-5L™ questionnaire.

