### Statistical methods

Demographics, patient, and tumour characteristics will be presented for each treatment arm. Continuous data will be reported as mean (standard deviation) or median (interquartile range or 95 per cent confidence interval), depending on the distribution. Categorical data will be reported as count with percentage. All statistical tests will be two-sided and *P* < 0.050 will be classified as statistically significant. Patients initially randomized but considered ineligible afterwards, based on information that should have been available before randomization, will be excluded from all analyses.

Analysis of the primary endpoint of this study, the proportion of patients with an R0 resection, will be based on the intention-to-treat principle using Fisher’s exact test. In addition, a per-protocol analysis will be performed as a sensitivity analysis.

All survival curves will be constructed according to the Kaplan–Meier method, and the log rank test will be used to compare treatment arms, adjusting for stratification factors at randomisation (previous radiotherapy, previous systemic therapy, and expert centre). In addition, hazard ratios will be calculated using a Cox proportional hazards regression model, adjusting for stratification factors. Metastasis-free survival, progression-free survival, and overall survival will be based on the intention-to-treat group. Local re-recurrence free survival and disease-free survival analyses will include only patients who underwent surgery.

Data on surgical characteristics, histopathological characteristics, and major surgical morbidity will be presented by treatment arm, and will be derived only for patients who underwent surgery. The number of patients undergoing surgery will be analysed in the intention-to-treat population. Comparison between treatment arms will be done by means of Fisher’s exact test.

The absolute and relative incidence of toxicities related to the administration of induction chemotherapy or chemoradiotherapy will be presented by treatment arm, and analysed in all patients who received at least one dose of neoadjuvant chemotherapy (experimental arm) or chemoradiotherapy (control arm). Comparison between treatment arms will be done by means of Fisher’s exact test.

Comparison of health-related quality of life between the two treatment arms at baseline and over time will be performed by means of a random-effects regression model and will be based on the intention-to-treat group.

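### The quality-of-life model compares the arms at baseline, where any difference can only be chance, and as worded it gives a less precise follow-up comparison than the collected data allow

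*Protocol article*

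**What the plan says.** The protocol article gives the quality-of-life analysis one sentence, under Statistical methods: "Comparison of health-related quality of life between the two treatment arms at baseline and over time will be performed by means of a random-effects regression". The same sentence adds that the analysis "will be based on the intention-to-treat group". It names no covariates, no specific contrast and no structure for the baseline means.

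The Questionnaires section sets the timing: "Patients will receive questionnaires at inclusion, and 3 and 12 months after surgery either by mail or digitally". That is one baseline and two follow-up occasions for QLQ-C30, QLQ-CR29 and EQ-5D-5L. In Tables 1 and 2 the first questionnaire is ticked in the column headed "Before allocation". The Outcomes section lists quality of life among the secondary outcomes.

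Statistical methods also sets a general rule, "All statistical tests will be two-sided", with significance at P below 0.050. For demographics, patient and tumour characteristics it plans only presentation by arm, without a comparison.

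**The concern.** A score taken before allocation has the same expected value in both arms. Comparing the arms at baseline therefore examines a null hypothesis that randomization has already made true. Under the general testing rule, about 5% of such tests come out significant by chance, and readers may take that as a meaningful imbalance.

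The second consequence concerns the comparison that matters. For one random-effects model to compare the arms at baseline and over time, it needs a free arm effect at the baseline occasion. The follow-up comparison then becomes either the raw difference at the visit or the difference in change from baseline. Neither makes full use of the knowledge that the baseline means are equal, so the intervals are wider than necessary.

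Quality of life is the main patient-reported evidence on the possible drawbacks of induction chemotherapy that the Introduction lists (toxicity, poorer performance status, surgical morbidity). Precision is already limited. Questionnaires need separate consent, and the follow-up forms are timed from surgery, which the Sample size section expects a quarter of patients not to reach.

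**Working it through.** **The plan's own figure.** The article states no effect size, standard deviation, correlation or power for quality of life. Its only sample-size figure concerns the R0 rate, and it reproduces:

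n = [1.96·√(2·0.525·0.475) + 0.8416·√(0.45·0.55 + 0.60·0.40)]² / 0.15² = 172.8, so 173 per arm (power 0.8005).

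346/0.95 = 364.2, stated as 364. This has no bearing on the quality-of-life point, except that 173 per arm sets a scale below.

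**Inputs.**
- One baseline and two follow-up scores (Questionnaires; Tables 1 and 2).
- 1:1 allocation (Study design and setting).
- Two-sided 5% tests (Statistical methods).
- *Assumed, not in the documents:* correlation ρ between baseline and follow-up scores of 0.3 to 0.7, compound symmetry, standard deviation 1 at each visit, complete data.

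**Formulas.** For one follow-up visit, the variance of the arm contrast, in units of 2/n with n per arm, is:
- follow-up contrast, free baseline arm effect: 1
- change contrast, free baseline arm effect: 2(1 − ρ)
- baseline adjusted, or baseline means constrained equal: 1 − ρ²

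The ratios to the adjusted variance are therefore 2(1 − ρ)/(1 − ρ²) = 2/(1 + ρ) for change and 1/(1 − ρ²) for follow-up.

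| ρ | Follow-up | Change | Adjusted | Change/adjusted | Follow-up/adjusted |
|---|---|---|---|---|---|
| 0.3 | 1.00 | 1.40 | 0.91 | 1.54 | 1.10 |
| 0.5 | 1.00 | 1.00 | 0.75 | 1.33 | 1.33 |
| 0.7 | 1.00 | 0.60 | 0.51 | 1.18 | 1.96 |

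A generalized least squares calculation for the three-occasion model gives the same ratios. Both exceed 1 for every ρ strictly between 0 and 1. For the mean of the two follow-up visits at ρ = 0.5, the variance is 0.75 for either unadjusted contrast and 0.50 adjusted, a ratio of 1.50.

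**In terms of power.** Take a comparison that would have 80% power unadjusted; this starting point is hypothetical. Adjusted power is Φ(2.802·√ratio − 1.96). At ρ = 0.5: Φ(2.802·√1.333 − 1.96) = 89.9%. For ρ = 0.3, 0.5 and 0.7 it is 93.5, 89.9 and 86.0% against the change contrast, and 83.6, 89.9 and 97.5% against the follow-up contrast.

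**In terms of detectable difference, ρ = 0.5, one visit, 80% power.**
- 173 per arm: the standard error falls from √(2/173) = 0.108 to √(2·0.75/173) = 0.093. Multiplied by 2.802, the detectable difference falls from 0.30 to 0.26 SD.
- About 130 per arm (0.75 × 173 = 129.75, if a quarter do not reach surgery, before losses from separate consent): from 0.35 to 0.30 SD.

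**The case against.** The strongest objection is that a reader might infer that the plan rejects baseline adjustment. The documents do not support that. The sentence neither states nor excludes a baseline covariate, and this is a condensed article whose full protocol and analysis plan are not shown. The fixed effects of a secondary longitudinal model are commonly specified there. This limits the point to what the sentence does commit to, namely an arm comparison at baseline within the model. That commitment implies a free baseline arm effect, and a model that constrains or conditions on baseline cannot deliver it.

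Other stronger readings also fail:
- *The treatment effect is diluted to two thirds.* This would follow from a single arm effect pooled over all three occasions. Such a model could not compare the arms both at baseline and over time, so it does not fit the sentence.
- *The missing stratification factors are an error.* The Interventions section says "Patients will be stratified for previous chemotherapy, previous radiotherapy, and expert centre", and the survival analyses adjust for these factors. Not repeating them for quality of life is an omission that an article may leave to the full protocol.
- *The large power gains are the expected loss.* The 97.5% comes from a raw follow-up contrast at ρ = 0.7. The natural reading of a comparison over time is change from baseline, where the gain at that correlation is from 80 to 86%. At ρ = 0.8 the excess variance is only 2/1.8 − 1 = 11%.
- *The baseline score adds nothing to the follow-up contrast.* This holds only with complete data, which are not to be expected here.
- *Any significant baseline difference is false by construction.* The same table column also ticks randomization itself, and forms may be sent by mail or digitally in an open-label trial. Completion before allocation is the likely reading, but the article does not expressly fix it for every form.

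**Conclusion.** The point stands in a limited form. With the first questionnaire listed before allocation, a between-arm comparison at baseline can show only chance. A model with a free baseline arm difference gives an unbiased follow-up comparison, but a less precise one than the data permit. At one follow-up visit the variance is 18 to 54% too large for the change contrast and 10 to 96% too large for the follow-up contrast over ρ = 0.3 to 0.7; at ρ = 0.5 it is 33% for both, about 15% in standard error.

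These sizes rest on an assumed correlation, compound symmetry and complete data. The direction of the loss does not depend on which ρ between 0 and 1 is chosen. The issue is one of efficiency and of interpreting a baseline test, for a secondary outcome. The R0 analysis and the sample size are untouched.

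**What to change.** Replace the sentence with wording such as: *Baseline quality-of-life scores will be described by arm without a test. Arms will be compared at 3 and 12 months after surgery with a longitudinal random-effects model that includes baseline as an occasion with arm means constrained to be equal, visit, and arm-by-visit effects at follow-up.*

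This version keeps patients without an inclusion questionnaire and so fits the stated intention-to-treat group. Entering the baseline score as a covariate is an acceptable alternative, at the small cost of losing those patients; with missing baseline forms the two versions are not the same analysis. The analysis plan should also state that the inclusion form is completed before randomization, because the equality constraint rests on it.

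The cost is a short text change. No new data are needed, since the inclusion questionnaire is already collected.

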### Data collection and management

A central study database (Netherlands Comprehensive Cancer Institute (IKNL), Utrecht, the Netherlands) with an electronic case report form will be used to record all data required to address the primary and secondary objectives. Local data management will be undertaken by the IKNL or an in-hospital qualified local data management team. Questionnaires will be collected centrally by the coordinating investigators and recorded using an ISO 27001-certified information security system (Research Manager, Deventer, Netherlands).

### Data safety monitoring board

A central data safety monitoring board (DSMB), consisting of a medical oncologist, a surgical oncologist, and a statistician, has been assigned to monitor the safety of study participants, and to protect the validity and credibility of the study. Members of the DMSB are independent and have no competing interest. After 100 patients have undergone surgery, the DSMB will review the safety data. Inclusion will be continued during interim analysis. At the interim analysis, the number of patients who cannot complete the full course of chemoradiotherapy and the number of patients with major postoperative morbidity (Clavien–Dindo grade at least III) will be tabulated and discussed. Examining these safety and logistical aspects will not affect the total sample size or the actual α level at final analysis. After the interim analysis, the DSMB will recommend to the trial steering committee (TSC) whether the study should be continued or terminated. Should the TSC decide not to fully implement the advice of the DSMB, it must explain to the medical ethical committee why (part of) the advice of the DSMB will not be followed.

### Harms

All serious adverse events (SAEs) or suspected unexpected serious adverse events (SUSARs) will be reported by the physician to the study coordinator within 24 h and without undue delay after obtaining knowledge of the event. The coordinating investigator will report SAEs through the web portal ToetsingOnline (https://www.toetsingonline.nl) to the medical ethical committee that approved the protocol. The time window for recording SAEs and SUSARs is from randomization until 3 months after surgery, or 1 month after the last day of neoadjuvant treatment for patients with progressive disease who did not undergo surgery. SAEs and SUSARs will be followed up until resolved or until a stable situation has been reached.

### Auditing

The study will be monitored by independent qualified monitors. The monitoring plan is based on the assessment that the study carries a moderate risk for the participants.

### Research ethics approval

This study was approved by the Medical Research Ethics Committees United, Nieuwegein, the Netherlands (R20.035), the Dutch Competent Authority (Centrale Commissie Mensgebonden Onderzoek, The Hague, the Netherlands; NL73593.100.20), and all institutional review boards of the participating study centres. The study will be submitted to the competent authorities, central ethical committees, and institutional review boards of the participating international centres.

### Protocol amendments

All substantial amendments will be notified to the (principal) investigators, institutional review boards of all study centres, the medical ethical committee, the competent authority, and trial registries.

### Consent and assent

Informed consent will be obtained by the treating physician in one of the expert centres. Patients will be allowed to provide separate permission for the collection of blood and/or tissue samples for translational research, and for receiving quality of life questionnaires.

### Confidentiality

Individual patient information obtained as a result of this study is considered confidential and its handling will conform with the Dutch Personal Data Protection Act (AVG). Patients’ confidentiality will be ensured by use of study numbers.

### Access to data

Access to the final data set is reserved for the central data manager, study statistician, coordinating investigator, and trial steering committee. There are no contractual agreements that limit this access.

### Ancillary and post-study care

The study has no provision for ancillary or post-study care.

### Dissemination policy

The results of this study will be dispersed by publishing the results in international peer-reviewed journals and by offering an abstract to international (surgical) oncological congresses. Any publication, abstract or presentation based on patients included in this study must be approved by the trial steering committee and coordinating investigator. The principal manuscript resulting from this study will be published by group authorship (PelvEx Collaborative).

## Discussion

This randomised controlled trial will investigate the role of induction chemotherapy in patients with LRRC. The results of this study will demonstrate whether or not induction chemotherapy has additional value in the treatment of patients with non-metastasized resectable LRRC with regard to the R0 resection rate; this group of patients has had a poor prognosis so far.

The rationale for R0 resection as the primary outcome in this study was based on the fact that R0 resection is the most important prognostic factor for survival in patients undergoing surgery for LRRC. Ultimately, an increase in R0 resection rate should lead to an improvement in local re-recurrence-free and overall survival. Because of the relatively rarity of LRRC as a result of improvements in the treatment of primary rectal cancer, and the fact that approximately 50 per cent of patients with LRRC will not be eligible for inclusion in this study owing to distant metastases or unresectable local disease, survival parameters could not be used as the primary outcome, as power calculations showed that the sample size would be unfeasible^42^^,^^43^.

The rationale for the induction chemotherapy regimen chosen in this study is based on studies in (metastatic) colorectal cancer. In those first-line studies^44–47^, doublet therapy led to better response rates and improved survival compared with monotherapy. Results of triplet therapy among patients with metastatic colorectal cancer have been conflicting^48^^,^^49^. In addition, although higher response rates have been observed for triple therapy compared with doublet therapy in patients with right-sided metastatic colorectal cancer, this has not been observed in patients with left-sided disease^50^^,^^51^. Moreover, triplet therapy is associated with more toxicity, and in patients with LRRC, in particular, toxicity of treatment is considered a major limitation often precluding curative treatment^52^. Therefore, doublet therapy is the treatment regimen of choice. As doublet therapy with capecitabine and oxaliplatin (CAPOX), 5-fluorouracil, leucovorin, and oxaliplatin (FOLFOX), and 5-fluorouracil, leucovorin, and irinotecan (FOLFIRI) have similar efficacy, all are incorporated in the present study protocol^46^^,^^53^^,^^54^.

There are three other ongoing trials investigating the optimal treatment for patients with LRRC. The French GRECCAR15 study (Chemotherapy Followed by Pelvic Reirradiation Versus Chemotherapy Alone as Pre-operative Treatment for Locally Recurrent Rectal Cancer; NCT03879109) is randomizing between induction chemotherapy, chemoreirradiation, and surgery *versus* induction chemotherapy and surgery in previously irradiated patients. The primary outcome measure is the R0 resection rate. The Japanese JCOG1801 study (Surgery Plus Chemo Versus Chemoradiotherapy Followed by Surgery Plus Chemo for Locally Recurrent Rectal Cancer; NCT04288999) is randomizing between surgery followed by adjuvant chemotherapy *versus* neoadjuvant chemoradiotherapy, surgery, and adjuvant chemotherapy (CAPOX/FOLFOX) in radiotherapy-naive patients, with local recurrence-free survival as the primary outcome measure. The Chinese NARC study (Efficacy and Safety Study of Neoadjuvant in Treating Patients With Resectable Local Recurrent Rectal Cancer; NCT01271192) is randomizing between surgery followed by adjuvant chemotherapy *versus* neoadjuvant chemoradiotherapy, surgery, and adjuvant chemotherapy, with overall survival as the primary outcome measure. The results of these studies will be actively monitored to assess whether their results have any implications for the present study protocol.

